## **Exclusion criteria**

- Previous failure of antiretroviral therapy, understood as a rebound in viral load that can be detected after having reached undetectable levels. Low-grade increases (<200 copies of HIV RNA/mL) and transitory increases (blips) resolved without modifying antiretroviral therapy are excluded.
- Proven resistance against the antiretroviral drugs under study.
- Planned interruption of antiretroviral therapy.
- Taking immunosuppressive or immunostimulating medication of any type, including valproic acid.
- Taking a fusion inhibitor (enfuvirtide).
- Pregnancy or intention to become pregnant during the study.

## **Number of subjects planned and rationale**

As this is a pilot study, the minimum number of patients necessary to prove the concept has been estimated in 10.

## **Analysis and withdrawal criteria**

The patient can decide to withdraw from the study at any time. The investigator can also decide to withdraw a patient if the patient does not fulfill the norms of the protocol. Virological failure or development of toxicity to any of the study drugs will also be a reason for leaving the study.

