## **Study development**

Patients who fulfill the inclusion criteria will undergo the following procedures:

- Clinical history including duration of antiretroviral therapy and demonstrated period of undetectable viral load.
- Complete physical examination including height, weight, and temperature.
- Heart rate and systolic and diastolic blood pressure.
- Blood count, biochemistry, and urinalysis as described in section 8.3.2 of this protocol. Women will undergo a pregnancy test.
- Determination of viral load using ultrasensitive methods and CD4+ T lymphocyte count in blood samples.
- Determination of viral tropism.
- Measurement of the size of the reservoir of latent virus and its reactivation capacity.

Blood samples will be extracted by conventional phlebotomy on the dates set out in the study time line. The determinations will be carried out in the study center, with the exception of the determination of viral tropism and measurement of the size of the latent reservoir. For the former, samples will be sent to the Monogram® laboratories in the United States of America, as this is the only laboratory in the world approved for phenotyping coreceptors. For the latter, the samples will be taken in two laboratories: Infectious Diseases Laboratory from Hospital Ramón y Cajal and to the Molecular Immunobiology Laboratory of the Hospital General Universitario Gregorio Marañón (Dra. [name]) in Madrid.

After inclusion each patient receives, in addition to their usual medication, a CCR5 coreceptor antagonist entry inhibitor (maraviroc) in a dose of 150-600 mg every 12 hours according to technical data and previous treatment.

Treatment will be administered for at least 12 months. During this period, viral load will be measured using ultrasensitive methods, the CD4 count will be determined in peripheral blood, and the size of the reservoir of latent virus will be measured every 3 months after a blood extraction of 350 of total blood. After the intensification period with maraviroc and after drug suspension, patients will be following up during two additional visits according the study plan.

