**STUDY PLAN**

| ***Day*** | ***Baseline***  ***1*** | ***Baseline 2*** | ***Month 3*** | ***Month 6*** | ***Month 9*** | ***Month 12*** | ***Month 15*** | ***Month 18*** |
| --- | --- | --- | --- | --- | --- | --- | --- | --- |
| **Informed consent** | X |  |  |  |  |  |  |  |
| **Clinical history** | X | X | X | X | X | X | X | X |
| **Physical examination1** | X | X | X | X | X | X | X | X |
| **Pregnancy test (women)** |  | X |  |  |  |  |  |  |
| **Determination of viral tropism** | X |  |  |  |  |  |  |  |
| **Inclusion criteria** | X |  |  |  |  |  |  |  |
| **Laboratory determinations2** | X | X | X | X | X | X | X | X |
| **Administration of drugs** |  | X | X | X | X | X |  |  |
| **Evaluation of adverse effects** |  | X | X | X | X | X |  |  |

1 Includes heart rate and blood pressure.

2 Includes blood count, biochemistry, habitual immunological and virological monitoring, as well as measurement of the size of the latent reservoir, residual viremia and immune activation markers.

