# ADVERSE EVENTS

## **Minimum required information**

The research team will follow up any adverse events that occur during the study. They will record the time of onset, the duration, intensity, course, and outcome of the event in order to evaluate the relationship of causality between the adverse event and the medication.

Recording of adverse events will be by a generic question of the following type: Have you noticed anything since you started taking the medication? or after spontaneous notification by the patient.

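### Section 5.4 does not separate stopping maraviroc from leaving the study, so early stoppers lose their remaining reservoir measurements; the Study plan also schedules no adverse-effect evaluation at Months 15 and 18

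*Protocol*

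**What the plan says.** **Leaving the study.** Protocol section 5.4 (Analysis and withdrawal criteria) states: "Virological failure or development of toxicity to any of the study drugs will also be a reason for leaving the study". It adds a discretionary ground: "The investigator can also decide to withdraw a patient if the patient does not fulfill the norms of the protocol". It describes no intermediate state in which a patient is off maraviroc but still attends visits.

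**Visits after drug.** Section 7.2 (Study development) states: "After the intensification period with maraviroc and after drug suspension, patients will be following up during two additional visits according the study plan". In the Study plan table, laboratory determinations are marked at every visit from Baseline 1 to Month 18. The footnote says that these cover routine bloods "as well as measurement of the size of the latent reservoir, residual viremia and immune activation markers".

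**Adverse events.** Section 8.1 (Minimum required information) states: "The research team will follow up any adverse events that occur during the study". It asks for the course and outcome of each event to be recorded. The Study plan row "Evaluation of adverse effects" is marked from Baseline 2 to Month 12 and is blank at Months 15 and 18. Section 8.2 (Imputability criteria) includes improvement once the drug is suspended among the conditions for its highest causality grade.

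**Analysis.** Section 11 plans random-effects regression of log10 IUPM on time, assumed linear, in a single group of 10, with no dropout allowance. Annex IV warns that in viraemic patients the culture assay also detects recently infected cells, at much higher frequencies than under suppressive therapy.

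**The concern.** The primary endpoint is reservoir size, and the estimate of interest is its slope over time. Under 5.4 a patient who fails virologically or develops toxicity exits, and reservoir sampling ends with the exit. A patient who does well is sampled on drug to Month 12 and off drug at Months 15 and 18. Which patients have later data therefore depends on how they fared.

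A random-effects model copes with dropout that the observed IUPM values explain. Here the exit triggers are plasma viral load and toxicity, and neither is in the model that section 11 describes. There is no control arm against which selective loss could be judged. A later analysis plan can choose how to handle missing values, but it cannot recover blood that was never drawn, so this has to be settled in the protocol.

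On safety, the two off-drug visits are where recovery after suspension would be seen. The visit table schedules no adverse-effect evaluation there.

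**Working it through.** The protocol gives no power calculation, dropout rate or standard deviation, so there is no planned figure to reproduce. The figures below only give scale.

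**1. Scheduled measurements lost (Study plan).** From Baseline 2, the reservoir is scheduled at Months 0, 3, 6, 9, 12, 15 and 18, which is 7 visits. Adverse-effect evaluation is scheduled at 5 (Months 0 to 12).
- Leaving after Month 3 loses Months 6, 9, 12, 15 and 18: 5 of 7.
- Leaving after Month 6 loses 4, and after Month 9 loses 3.

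**2. Chance that it happens.** With an assumed per-patient risk p of leaving, P(at least one of 10) = 1 - (1 - p)^10.
- p = 5%: 40%
- p = 10%: 65%
- p = 20%: 89%
- p = 30%: 97%

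Each leaver is 1/10 of the sample.

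**3. Background decay.** The protocol's background text (In vivo viral latency) cites a reservoir half-life of 44.2 months. Twelve-month change = -12 x log10(2)/44.2 = -12 x 0.00681 = -0.082 log10.

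**4. Illustrative shift.** Let k patients leave with a true 12-month change d (assumed; the documents give none), and let 10 - k follow background decay. True mean = [k x d - (10 - k) x 0.0817]/10. Those remaining show -0.082 throughout.

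With d = +0.30:
- k = 1: (0.30 - 0.735)/10 = -0.044
- k = 2: (0.60 - 0.654)/10 = -0.005
- k = 3: (0.90 - 0.572)/10 = +0.033

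With k = 2 and d varied:
- d = +0.15: (0.30 - 0.654)/10 = -0.035
- d = 0: (0 - 0.654)/10 = -0.065
- d = -0.30: (-0.60 - 0.654)/10 = -0.125

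The last line shows that the sign depends on d. If leavers' reservoirs fall faster than background, losing them biases the mean the other way.

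**5. What the planned model does to this.** Step 4 compares everyone with completers only. The random-effects model retains leavers' values up to exit, so where those values already show the rise, part of the shift is removed. The full shift is approached when a patient leaves before any post-baseline measurement, or when the rise begins only at or after exit. The gap of about 0.08 for k = 2 and d = +0.30 is therefore an upper bound for that assumption, not an estimate.

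**6. Passages side by side.**
- Section 7.2 promises two visits after drug suspension and could be read to include early suspension; section 5.4 says those patients leave. The two are not reconciled.
- Section 8.1 covers adverse events throughout the study; the Study plan schedules their evaluation only to Month 12, although patients attend at Months 15 and 18 for history, examination and laboratory tests.

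**The case against.** The strongest reply is that little is lost. Completers are measured off drug at Months 15 and 18, so a reader who infers that off-drug reservoir outcomes are missing altogether goes too far: only early leavers are affected. Nor do the documents support the inference that the outcome of toxicity leading to withdrawal goes unrecorded, because section 8.1 asks for course and outcome. History, examination, blood count and biochemistry also continue to Month 18. Withdrawal for not meeting the protocol's norms is at the investigator's discretion, so it is not an automatic exit. All of this stands. It narrows the point to early leavers and to a mismatch between the visit table and section 8.1.

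A second reply is that the direction of bias is not established. That stands for toxicity, where nothing in the protocol says which way the reservoir would move. For virological failure, a shift towards apparent decline is plausible: the background text describes a view in which ongoing replication helps to maintain the reservoir. It also reports the contrary view, so plausible is as far as it goes.

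A third reply concerns the remedy. One might infer that all later IUPM values belong in the primary slope. Annex IV argues against this: after failure the assay no longer isolates the latent reservoir, and in a sample of 10 a few high values could dominate. Section 11 also contains no time-varying term for being on or off drug, only an interaction of time with treatment received. This stands, and it is a reason to flag those values and show both analyses. It is not a reason to stop collecting them.

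**Conclusion.** The point holds in this limited form. Section 5.4 merges stopping maraviroc with leaving the study. An early stopper therefore forfeits up to five of the seven reservoir measurements scheduled from Baseline 2 (exit after Month 3), while completers are followed to Month 18. The loss is related to outcome, through triggers that the described model does not contain, and can bias the slope.

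The size is uncertain. With two leavers at an assumed +0.30 log10, the true mean change is -0.005 against -0.082 among those remaining. A reader might take this as a demonstrated artefact equal to a full year of background decay. The documents do not support that, because the +0.30 is not sourced in them and the model keeps pre-exit values. It is the ceiling for one assumption. The direction is plausibly towards decline for virological failure and unknown for toxicity.

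The safety part is a textual mismatch: the Study plan and section 8.1 disagree on whether adverse events are evaluated at Months 15 and 18, and section 8.2 relies on what happens after suspension. In an exploratory pilot reporting estimates without emphasis on P values, neither part is fatal. Both should be corrected, since unsampled visits cannot be recovered later.

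**What to change.** - **Section 5.4:** without changing when drug is stopped, state that stopping maraviroc for any reason is distinct from leaving the study. Early stoppers keep the remaining scheduled visits and measurements unless they withdraw consent.
- **Section 7.2:** reconcile the sentence on the two post-suspension visits with 5.4, so that it is clear what applies to early stoppers.
- **Section 11:** flag IUPM values obtained after virological failure and report the slope with and without them, citing the assay limitation in Annex IV.
- **Study plan:** mark the adverse-effects row at Months 15 and 18, in line with section 8.1.

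**Cost.** No visit is added to the schedule. Some early stoppers would go on attending and giving large blood samples: section 7.2 gives 350 with no unit and Annex IV gives 300 ml. That burden falls on patients who have just had toxicity or failure, and should be weighed and explained in the consent. The change needs an amendment reviewed by the ethics committee (section 10.5).

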## **Approximate duration of the enrollment period**

6 months.

# DESCRIPTION OF TREATMENT

## **Definition of treatment**

Maraviroc, tablets.

*Dose per subject*: 150 - 600 mg every 12 hours according technical data and previous treatment

*Route of administration*: Oral

## **Concomitant treatment**

The antiretroviral regimen that the patient had been taking and that must include at least 3 antiretroviral drugs (2 nucleoside reverse transcriptase inhibitors combined with a protease inhibitor or a non-nucleoside reverse transcriptase inhibitor).

# STUDY DEVELOPMENT AND EVALUATION OF RESPONSE

## **Evaluation criteria.**

The efficacy of the therapy administered will be evaluated by measuring the size of the latent reservoir of HIV-1. The frequency of resting CD4+ T cells infected by a replicative virus will be determined. The description of the samples and the technique to be used for their evaluation are included in Annex 4.

## **Study development**

Patients who fulfill the inclusion criteria will undergo the following procedures:

- Clinical history including duration of antiretroviral therapy and demonstrated period of undetectable viral load.
- Complete physical examination including height, weight, and temperature.
- Heart rate and systolic and diastolic blood pressure.
- Blood count, biochemistry, and urinalysis as described in section 8.3.2 of this protocol. Women will undergo a pregnancy test.
- Determination of viral load using ultrasensitive methods and CD4+ T lymphocyte count in blood samples.
- Determination of viral tropism.
- Measurement of the size of the reservoir of latent virus and its reactivation capacity.

Blood samples will be extracted by conventional phlebotomy on the dates set out in the study time line. The determinations will be carried out in the study center, with the exception of the determination of viral tropism and measurement of the size of the latent reservoir. For the former, samples will be sent to the Monogram® laboratories in the United States of America, as this is the only laboratory in the world approved for phenotyping coreceptors. For the latter, the samples will be taken in two laboratories: Infectious Diseases Laboratory from Hospital Ramón y Cajal and to the Molecular Immunobiology Laboratory of the Hospital General Universitario Gregorio Marañón (Dra. [name]) in Madrid.

After inclusion each patient receives, in addition to their usual medication, a CCR5 coreceptor antagonist entry inhibitor (maraviroc) in a dose of 150-600 mg every 12 hours according to technical data and previous treatment.

Treatment will be administered for at least 12 months. During this period, viral load will be measured using ultrasensitive methods, the CD4 count will be determined in peripheral blood, and the size of the reservoir of latent virus will be measured every 3 months after a blood extraction of 350 of total blood. After the intensification period with maraviroc and after drug suspension, patients will be following up during two additional visits according the study plan.

**STUDY PLAN**

| ***Day*** | ***Baseline***  ***1*** | ***Baseline 2*** | ***Month 3*** | ***Month 6*** | ***Month 9*** | ***Month 12*** | ***Month 15*** | ***Month 18*** |
| --- | --- | --- | --- | --- | --- | --- | --- | --- |
| **Informed consent** | X |  |  |  |  |  |  |  |
| **Clinical history** | X | X | X | X | X | X | X | X |
| **Physical examination1** | X | X | X | X | X | X | X | X |
| **Pregnancy test (women)** |  | X |  |  |  |  |  |  |
| **Determination of viral tropism** | X |  |  |  |  |  |  |  |
| **Inclusion criteria** | X |  |  |  |  |  |  |  |
| **Laboratory determinations2** | X | X | X | X | X | X | X | X |
| **Administration of drugs** |  | X | X | X | X | X |  |  |
| **Evaluation of adverse effects** |  | X | X | X | X | X |  |  |

1 Includes heart rate and blood pressure.

2 Includes blood count, biochemistry, habitual immunological and virological monitoring, as well as measurement of the size of the latent reservoir, residual viremia and immune activation markers.

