## **Description of the methods for evaluating the response**

### Laboratory determinations

Blood workup: red cells, hemoglobin, hematocrit, mean corpuscular volume, mean corpuscular hemoglobin, mean corpuscular hemoglobin concentration, platelets, leukocytes, and leukocyte formula.

Biochemistry: aspartate aminotransferase, alanine aminotransferase, LDH, alkaline phosphatase, GGT, total bilirubin, uric acid, creatinine, urea, calcium, phosphorus, glycemia, cholesterol, triglycerides, and albumin.

Pregnancy test.

CD4+ T lymphocyte count.

Determination of HIV viral load using ultrasensitive methods.

Evaluation of viral tropism, by phenotyping.

Measurement of latent reservoir of HIV-1 (see Annex IV)

Direct measurement of residual viremia using the real time PCR (SCA) and Episomal DNA circles with 2-LTRs (see Annex IV)

Immune Activation Markers as indirect measurement of residual viremia (see Annex IV)

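### The study plan schedules one pregnancy test, at Baseline 2, and none at Months 3, 6, 9 or 12 on maraviroc; adding them is a cheap, minor safety improvement

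*Protocol*

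**What the plan says.** The Study plan table in Protocol section 7.2 has eight visits: Baseline 1, Baseline 2 and Months 3, 6, 9, 12, 15 and 18. The rows that matter here are:

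- Pregnancy test: "Pregnancy test (women) | | X". There is one mark, at Baseline 2.
- Drug: "Administration of drugs | | X | X | X | X | X". The marks are at Baseline 2 and Months 3, 6, 9 and 12.
- History: "Clinical history | X | X | X | X | X | X | X | X". It is marked at all eight visits, as is physical examination.
- Adverse effects: "Evaluation of adverse effects | | X | X | X | X | X". The marks stop at Month 12.
- Laboratory determinations: marked at all eight visits. Footnote 2 defines the row: "Includes blood count, biochemistry, habitual immunological and virological monitoring, as well as measurement of the size of the latent reservoir", followed by residual viremia and activation markers. The pregnancy test is not among them.

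The text of section 7.2 says "Women will undergo a pregnancy test" in the list of procedures for eligible patients and gives no repeat. Of the drug it says "Treatment will be administered for at least 12 months". Section 7.3.1 lists "Pregnancy test" without a visit.

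Section 5.2 bars women who are pregnant or who plan a pregnancy while on study. Section 5.4 lets the patient leave at any time, lets the investigator withdraw a patient who does not meet the protocol's rules, and names virological failure and toxicity as further reasons. It does not name pregnancy.

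**The concern.** Section 5.2 shows that the sponsor does not want pregnancy during the study, and not only at entry. The protocol nevertheless fixes its only test on the day when drug starts, and treatment then runs for a year or more. A pregnancy that begins in that year and is not yet recognised would meet no scheduled test.

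Two exposures are at stake: continued maraviroc, and the repeated large blood draws for the reservoir assay. If a pregnancy is found, the text shown does not say what happens to either. This is a question of patient safety. The reservoir endpoint, the regression model and the reported estimates are not affected.

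**Working it through.** The protocol gives no formula for this point. The check is a count of the schedule, a reading of the other places where a test might be implied, and simple arithmetic on the proposed change.

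**1. Scheduled tests (Study plan, 7.2).**
- Tests per visit: 1 of 8.
- Visits with drug: 5, of which 1 has a test.
- Drug visits after the start: 5 − 1 = 4 (Months 3, 6, 9, 12), of which 0 have a test.

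**2. Could a repeat test be implied elsewhere?** Section 7.3.1 lists the test among the laboratory determinations, and the row of that name is marked at every visit. Footnote 2 says what that row contains and leaves the test out. A separate row with one mark would also serve no purpose if the test were done at every visit. The treatment-period measurements in section 7.2 are viral load, CD4 count and reservoir size. The single mark is therefore the schedule.

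**3. What else could find a pregnancy?**
- History and examination: 4 of the 4 later drug visits, and both visits after drug (Months 15 and 18).
- Adverse-effect evaluation: 4 of the 4 later drug visits, and 0 of 2 at Months 15 and 18. Under section 8.1 it relies on a general question or the patient's own report.
- Patient contact: section 10.1 has patients told to contact the investigators about any problem, and given the means to do so.

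All of these can find a recognised pregnancy. None is a test for an unrecognised one.

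**4. Blood drawn after the only test.** Annex IV uses 300 ml per reservoir measurement. Section 7.2 says 350 without a unit, taken here as ml (an assumption). Footnote 2 places the measurement at every visit, so six draws follow Baseline 2 (Months 3 to 18):
- 6 × 300 = 1,800 ml, or 6 × 350 = 2,100 ml.

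**5. Size of the change.** Let w be the number of women of childbearing potential. It is not stated, so w runs from 0 to 10.
- Months 3, 6, 9 and 12: 4 × w = 0 to 40 tests.
- One more test each if drug continues past Month 12: up to 1 × 10 = 10, so at most 50 in all.

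**6. Delay to detection with the change.** Tests would be 3 months apart. If conception is equally likely on any day (an assumption), the wait to the next scheduled test is 0 to 3 months, with mean 3/2 = 1.5 months. That is the time to a test, not to a positive result. If a test stays negative for the first d months after conception (d is not given in the protocol), the delay to a positive scheduled test runs from d to 3 + d months, with mean 1.5 + d. A conception within d months of the last scheduled test would not be caught by scheduled testing at all.

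**The case against.** The strongest reply is that nothing is wrong. Section 5.2 is an entry criterion, and the Baseline 2 test checks it at the right moment. No part of the protocol sets a testing frequency that the plan fails to meet. The protocol states no pregnancy risk for maraviroc. The consent form, investigator brochure and case report form are not shown and may carry contraception or pregnancy instructions. History and examination take place at all four later drug visits, patients are told to report problems (10.1), the investigator has discretion to withdraw a patient (5.4), and section 8.2 counts a congenital anomaly among severe reactions.

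Much of this stands. A reader might infer that the schedule contradicts section 5.2. It does not: an eligibility rule needs a check at entry, and there is one. A reader might also infer that pregnancy on drug would go unmanaged or that contraception was overlooked. The documents do not support that either, because discretionary withdrawal exists and the pages where such instructions would normally sit are missing from the review copy.

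What the reply does not remove is the schedule itself. The timing is not left open for another document to fill: a dedicated row fixes it at one visit. Contraception advice would lower the risk but would not add a test. The entry criterion also looks ahead to pregnancy on study, so a later pregnancy is a concern that the protocol itself raises.

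**Conclusion.** The point holds as a minor, low-cost safety improvement. It is not an inconsistency, and it has no statistical consequence. None of the 4 drug visits after the start carries a pregnancy test, so a pregnancy not recognised clinically could continue under maraviroc and large-volume draws until symptoms, examination or the patient brought it to light.

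The size of the benefit cannot be fixed from the protocol. It depends on how many women of childbearing potential enrol (0 to 10), on how often a pregnancy would escape history and examination, and on what the unseen documents instruct. If no such women enrol, the effect is nil. The conclusion assumes only that the table's dedicated row is the operative schedule, which footnote 2 supports.

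**What to change.** - Keep the Baseline 2 test and require its result before the first dose.
- Add a pregnancy test for women of childbearing potential at Months 3, 6, 9 and 12, run on the blood already drawn. If drug continues past Month 12, add one at the end of treatment, since the Month 12 test cannot cover later exposure.
- Name pregnancy in section 5.4 as an event that requires a decision on stopping maraviroc and the reservoir draws.

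The cost is the small price of 0 to 40 tests, or at most 50 if treatment is extended in everyone. There is no new visit, no extra needle stick and no change to the analysis.

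Two limits remain. A conception shortly before a visit can test negative and wait for the next test, so undetected exposure can somewhat exceed 3 months. A test run on a visit's blood also cannot prevent that visit's draw, only later ones.
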